#### Secondary analyses

To test the difference across time between the two conditions (minimal or extended Internet-based intervention), a group (1, 2) x time (0, 6, 12, and 24) repeated measures MANOVA will be performed, including the primary outcome variable (AUDIT-C) and the two secondary outcome drinking variables (number of drinks in a typical week and greatest number of drinks on one occasion). Missing data will be replaced using a maximum likelihood approach. Planned contrasts will determine the nature of the differences observed. These planned contrasts will be stepped such that significant differences must be observed at the six months’ time point before comparisons will be made between condition at the twelve months’ time point, etc. Effect sizes will be calculated to determine the magnitude of differences in standard units. Interaction terms will be added to the MANOVA to test for sex differences (i.e., is there an interaction effect of subjects’ sex by experimental condition on drinking outcomes?). Finally, a separate repeated-measure ANOVA will be employed to test the hypothesis on the impact of receiving access to the Internet-based interventions on Health Related Quality of Life (secondary hypothesis 3). As part of these secondary analyses, we will also conduct a chi-square test to explore whether there is differential loss to follow-up between experimental conditions.

The proportion of each group that has sought further treatment (total and categorized into type of treatment such as support groups, residential, individual counseling) will be compared using χ^2^ statistics. If the proportion of treatment-seekers is high then further analyses will be conducted to explore the significance of this treatment to outcome.

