### Hypotheses

#### Primary hypothesis

Participants in the extended Internet intervention condition will display significantly improved drinking outcomes at twelve months compared to participants in the minimal Internet intervention condition.

Secondary Hypotheses:**Secondary Hypothesis 1**: Participants in the extended Internet intervention condition will display significantly improved drinking outcomes at six months compared to participants in the minimal Internet intervention condition.**Secondary Hypothesis 2**: Participants in the extended Internet intervention condition will display significantly improved drinking outcomes at two years compared to participants in the minimal Internet intervention condition.**Secondary Hypothesis 3**: Participants in the extended Internet intervention conditions will display significantly improved health-related quality of life at twelve months compared to participants in the minimal Internet intervention condition.**Secondary Hypothesis 4**: Participants in the extended Internet intervention condition who have more involvement with the AHC intervention between baseline and twelve-month follow-up will demonstrate more improvement in drinking outcomes at twelve-month follow-up, compared to respondents in the extended Internet intervention condition who have less involvement with the AHC intervention.

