#### Analysis plan: primary hypothesis testing

The primary hypothesis is that participants in the extended Internet intervention condition will display significantly improved drinking outcomes at twelve months compared to participants in the minimal Internet intervention condition. This will be tested for the primary outcome variable, the AUDIT-C, using an analysis of covariance with experimental condition as the between subject variable and the baseline value of the outcome variable as the covariate. A maximum likelihood approach will be used to replace any missing data at twelve-month follow-up. Sensitivity analyses will be conducted with participants lost to follow-up excluded.

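### The secondary drinking analysis treats baseline as a fourth time level and not as a covariate, so its valid 6- and 24-month contrasts are less precise than they could be

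*Protocol article*

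**What the plan says.** Under Secondary analyses, the protocol article gives the aim as "To test the difference across time between the two conditions" and states that "a group (1, 2) x time (0, 6, 12, and 24) repeated measures MANOVA will be performed". The model takes three outcomes together, "including the primary outcome variable (AUDIT-C) and the two secondary outcome drinking variables (number of drinks in a typical week and greatest number of drinks" (the last of these counted at a single sitting). It then adds that "Planned contrasts will determine the nature of the differences observed". These contrasts run in order of time: "These planned contrasts will be stepped such that significant differences must be observed at the six months" visit before twelve months is examined, and so on. Missing values are to be replaced by a maximum likelihood approach, and a sex interaction is to be added to the same MANOVA.

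Under Analysis plan: primary hypothesis testing, the 12-month AUDIT-C is analysed differently, "using an analysis of covariance with experimental condition as the between subject variable and the baseline value of the outcome variable as the covariate".

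Under Hypotheses, Secondary Hypotheses 1 and 2 are claims about single time points, six months and two years. The second reads that the extended arm "will display significantly improved drinking outcomes at two years compared to participants in the minimal Internet intervention condition".

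**The concern.** Time 0 precedes randomisation, so the two arms differ there only by chance. A standard group-by-time model does not use that knowledge. It estimates the baseline difference freely, as if it were another outcome. A contrast at a follow-up time then takes one of two forms. It may subtract the baseline difference in full (a change-from-baseline comparison), or it may ignore baseline (a plain follow-up comparison). Analysis of covariance subtracts only the part of the baseline difference that predicts the follow-up value, and so has the smaller variance.

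What is at stake is precision, not bias. It matters most at two years, where the article allows for the largest loss to follow-up and yet intends to detect an effect similar to the one planned for at twelve months. There is also an inconsistency: the 12-month AUDIT-C comparison is made once with baseline as covariate and again as a step in the MANOVA contrasts, by methods of different precision.

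**Working it through.** **Inputs from the article (Power analysis).** Difference 1 AUDIT-C point; SD 3.0 (pilot 2.5); significance level .05; power 80%; required final sample 286 (143 per condition); 480 recruited; 40% loss allowed at two years.

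**Assumed.** The correlation r between baseline and follow-up is not given, so a range is used. The SD is taken as equal at baseline and follow-up. Tests are two-sided, which is what reproduces the article's sample size.

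**The article's own figures.** A two-sided t-test with effect 1/3 SD and 80% power needs 142.25 per arm, hence 143 per arm and N = 286, as stated. Allowing for 40% loss, 286 / 0.6 = 477, which 480 covers. The expected number at two years under that allowance is 480 × 0.6 = 288, or 144 per arm.

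**Variance of each contrast, per participant:**
- follow-up only: SD²
- change from baseline: 2 × SD² × (1 − r)
- baseline as covariate: SD² × (1 − r²)

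The third is smaller than the second for every r below 1, and smaller than the first for every nonzero r. The ratio of the third to the second is (1 − r²) / [2(1 − r)] = (1 + r)/2. The standard error of a change contrast is therefore √[2/(1 + r)] times that of the adjusted contrast.

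**Example at r = 0.5.** Change: 2 × 9 × 0.5 = 9, the same as ignoring baseline. Covariate: 9 × 0.75 = 6.75, which is 25% lower. With 144 per arm the standard errors are √(9 × 2/144) = 0.354 and √(6.75 × 2/144) = 0.306.

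**Two-year power, 144 per arm, difference 1, SD 3 (t-based; a normal approximation differs by at most 0.003):**

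| r | Follow-up only | Change from baseline | Baseline as covariate | SE ratio, change to covariate |
|---|---|---|---|---|
| 0.3 | 0.805 | 0.664 | 0.840 | 1.24 |
| 0.4 | 0.805 | 0.730 | 0.868 | 1.20 |
| 0.5 | 0.805 | 0.805 | 0.902 | 1.15 |
| 0.6 | 0.805 | 0.883 | 0.941 | 1.12 |
| 0.7 | 0.805 | 0.953 | 0.977 | 1.08 |
| 0.8 | 0.805 | 0.994 | 0.997 | 1.05 |

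Below r = 0.5 the change contrast is less precise than ignoring baseline altogether, and it falls under the 80% target.

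**At the pilot SD of 2.5**, same numbers per arm and r = 0.3/0.4/0.5: follow-up only 0.923 throughout; change 0.816/0.870/0.923; covariate 0.944/0.958/0.974. All exceed 80%, and the ordering is unchanged.

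**The case against.** The strongest reply is that this is an efficiency preference about a valid secondary analysis. Much of it stands.

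- **The hypotheses are tested.** A reader might infer that the MANOVA tests no stated hypothesis, or that Secondary Hypotheses 1 and 2 go untested. The article does not support that. It names between-condition contrasts at successive time points, and these carry a direction. The Pilot study section also states a hypothesis that reductions are better sustained with the extended intervention, which a group-by-time test can serve.
- **Dilution.** A reader might also infer that a real effect is shrunk to three quarters of its size by averaging over four waves. That would apply to a group main effect, but the article does not name the main effect as the test of interest. It asks about difference across time and then about single time points.
- **The size is assumed.** The correlation is not given, and at 0.7 or more the loss against a change score is slight. The SD of 3.0 is deliberately cautious. The 288 comes from an allowance, not a forecast, and maximum likelihood may also draw on participants with earlier visits.
- **The contrast form is not stated.** A condensed article may leave that to the analysis plan. A model constrained to equal baseline means could recover most of the lost precision.

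The last point does not remove the concern. The choice of time 0 as a level is stated, no such constraint is mentioned, and replacing missing values by maximum likelihood does not supply one. Both ordinary forms of the contrast lose precision against the method that the article already uses for its primary test.

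**Conclusion.** The point holds as a worthwhile, inexpensive improvement and not as an error that invalidates anything. The secondary drinking contrasts as described are unbiased under randomisation but less precise than baseline-adjusted ones. Across r = 0.3 to 0.7, at 144 per arm and SD 3, adjustment raises two-year power by about 0.04 to 0.17 over an unadjusted comparison (0.840 to 0.977 against 0.805). Over a change score the gain runs from 0.18 at r = 0.3 down to 0.02 at r = 0.7.

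The direction of the comparison does not depend on the assumptions; its size does. It rests on an assumed correlation, equal SDs over time, the article's cautious SD and its 40% loss allowance. The 12-month primary analysis and the sample size of 286 are not affected.

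**What to change.** Replace the MANOVA with one model for each drinking outcome (AUDIT-C, drinks in a typical week, highest number on one occasion):

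- Model the 6-, 12- and 24-month values by maximum likelihood, with that outcome's baseline as covariate, condition, time, condition × time, and an unstructured covariance.
- Test Secondary Hypotheses 1 and 2 as the 6-month and 24-month condition contrasts. The condition × time term remains available for the question of sustained effect.
- State the multiplicity rule for these contrasts across outcomes and times, including whether the stepped order is kept and how it runs for each outcome.
- Fit the sex × condition interaction as a separate additional model, so that it does not change what the main contrasts estimate.

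The change needs analysis wording only and no new data. The downside is that the single multivariate p-value is lost. Three outcomes at two hypothesised time points make six contrasts, so multiplicity must be handled explicitly and can no longer be left to the omnibus test.

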### Participants – inclusion and exclusion criteria

Participation in the trial will be restricted to those who are 19 and above (legal drinking age in Canada), current problem drinkers (as indicated by a score of 8 or more on the Alcohol Use Disorder Identification Test - AUDIT) [28,29], have home access to the Internet and read English (the AHC is currently only available in English). It should be noted that this recruitment procedure may result in the participation of some individuals who are dependent on alcohol. However, as Heather p. 366, [30] has well summarized, “evidence shows that brief interventions are effective and should be used for individuals who are not actively seeking help at specialist agencies. This justification is again independent of level of seriousness, although most recipients of community-based interventions will obviously have problems of a less severe variety.” Indeed, as respondents in this trial will not be treatment seekers, the IBIs could easily serve as their first exposure to any services for alcohol problems. Thus, it is appropriate to include all eligible individuals in this evaluation, no matter the severity of their problems. Further it is also possible that some respondents will have accessed addictions treatment or other forms of assistance for alcohol problems (such as Internet-based interventions) at some point in their lives. This will be assessed on the baseline questionnaire, however respondents will not be excluded from the study due to prior treatment access because the intent is to evaluate the impact of the interventions in the extended range of potential community participants. However, random assignment to condition should ensure that socio-demographic characteristics, such as treatment access, will be randomly assigned across conditions.

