#### Secondary outcome measure

Secondary outcome measures are: (1) number of drinks in a typical week [39-41]; and (2) highest number of drinks on a single occasion. Finally, Health related Quality of Live (HRQOL) will be measured at each time point using the WHOQoL-8. This short form has been used in a number of countries, is robust psychometrically, and overall performance is strongly correlated with scores from the original WHOQoL [42].

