### Data analysis

#### Power analysis

The AUDIT-C measure is employed in this power calculation because this scale is a well-validated screener that has research supporting the amount of change that is needed in order to be clinically significant. Ideally, the study should be powered to be able to detect a difference in 1 point on the AUDIT-C scale as this was the added impact of the extended intervention over the minimal intervention observed in a previous pilot study (albeit at a six-month follow-up). A reduction from 9 points to 8 points on the AUDIT-C scale is also a clinically significant effect, representing 15% fewer people drinking beyond recommended low risk guidelines and a five drink per week reduction in typical weekly consumption (findings from the 2009 CAMH Monitor, a general population survey of Ontario residents) [43]. Further, a relatively variable sample is assumed with a standard deviation of 3.0 units on the AUDIT-C (standard deviation in the pilot trial was 2.5).

Following the convention that studies should be designed to have a statistical power of at least 80%, and that hypotheses be tested at the .05 level of significance, these specifications resulted in a final sample (required after attrition) of N = 286 (143 participants per condition).

In addition, there is allowance for the possibility of a substantial loss to follow-up in order to ensure sufficient numbers for analyses. Further, while the power analysis was conducted referring to the primary hypothesis (12 months follow up), sufficient participants will be recruited in order to test for a similar effect size at the two-year time point. Specifically, there is an allowance for a 20% attrition at the one-year follow-up and 40% attrition at the time of the two-year follow-up, and proposing to recruit a total of 480 participants at baseline (thus, allowing for a possible 40% loss to follow-up at the two year time point).

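### The two drink-count outcomes are tested with baseline as a repeated level, not as a covariate, which costs their between-arm contrasts precision

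*Protocol article*

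**What the plan says.** The Secondary outcome measure section names two drinking outcomes besides AUDIT-C: drinks in a typical week and the "highest number of drinks on a single occasion". Under Secondary analyses, a group (1, 2) by time (0, 6, 12, 24) "repeated measures MANOVA will be performed, including the primary outcome variable (AUDIT-C") and, with it, "number of drinks in a typical week and greatest number of drinks on one occasion". Missing values are to be handled by maximum likelihood. Planned contrasts follow in steps: the arms are compared at twelve months only if six months was significant, and so on to the later visit.

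The section on primary hypothesis testing does something different. AUDIT-C at twelve months is analysed by ANCOVA with its own baseline as covariate.

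No baseline covariate, transformation or count model is named for the two counts. The text does not say that they will be analysed untransformed.

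**The concern.** In a group-by-time model whose time factor includes month 0, a between-arm contrast at a follow-up visit takes one of two forms. It may be the difference in change from baseline, which subtracts the whole baseline value. Or it may be the simple difference at the visit, which ignores baseline. ANCOVA subtracts the fraction of the baseline value that best predicts follow-up, so with randomised arms it is at least as precise as either in large samples. Maximum likelihood for missing values does not recover this gain while the baseline means are left free in each arm.

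The counts are the only secondary drinking outcomes, and they bear on secondary hypotheses 1 and 2 (six months and two years). The stepping adds to the loss: if a real six-month difference is missed, the comparisons at 12 and 24 months are not made.

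Skewness is a second, smaller matter. The eligibility section intends to "include all eligible individuals in this evaluation, no matter the severity of their problems", so a long right tail is likely in both counts, although the article gives no figures.

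**Working it through.** **The plan's own figure.** The Power analysis section wants to "detect a difference in 1 point on the AUDIT-C scale" with a "standard deviation of 3.0 units on the AUDIT-C", at the .05 level and 80% power. Two-sided, n per arm = 2(1.960 + 0.842)² × 3.0² / 1² = 141.3, so 142 per arm (284 in all). The t-based calculation gives 143 per arm, 286 in all, as stated. Allowing for 40% loss, 286 / 0.60 = 476.7, so 477 against the stated 480. The figure reproduces, but it concerns AUDIT-C only. No power is stated for either count.

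**Inputs for the counts**
- From the article: 1:1 allocation; 480 × 0.80 = 384 analysed at twelve months; 286 as the required minimum.
- Assumed, not in the article: mean 25 drinks a week at baseline; coefficient of variation (CV) 0.8 or 1.0; baseline to follow-up correlation ρ of 0.55 to 0.6; a 20% reduction in the extended arm; and, in the worked case, a 15% fall common to both arms. The 20% has an anchor: the article equates one AUDIT-C point with five drinks a week, and 5 / 25 = 20%.

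**Closed form.** Let s be the baseline SD and c·s the follow-up SD in an arm. The variance per person, in units of s², is:
- change from baseline: 1 + c² − 2ρc
- simple visit difference: c²
- ANCOVA: c²(1 − ρ²)

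Take CV 0.8 (s = 20), ρ = 0.55 and 192 per arm. With the 15% common fall, c = 0.85 in the minimal arm and 0.85 × 0.80 = 0.68 in the extended arm. The true difference is 0.20 × 21.25 = 4.25 drinks. Summing over the arms, SE = √(sum × 400 / 192), and power is approximately Φ(4.25 / SE − 1.96).

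| Contrast | Sum over arms | SE | z | Power |
|---|---|---|---|---|
| Change from baseline | 0.7875 + 0.7144 = 1.5019 | 1.769 | 2.403 | 67% |
| Visit difference | 0.7225 + 0.4624 = 1.1849 | 1.571 | 2.705 | 77% |
| ANCOVA | 1.1849 × 0.6975 = 0.8265 | 1.312 | 3.239 | 90% |

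The loss against ANCOVA is about 23 points for the change contrast and 13 for the visit difference. Put as sample size, the visit difference on 384 people is as precise as ANCOVA on 384 × 0.6975 = 268. The change contrast equals ANCOVA on 384 × 0.8265 / 1.5019 = 211.

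Without the common fall (c = 1 and 0.80, difference 5), the change contrast has sum 0.90 + 0.76 = 1.66, SE 1.860, z 2.689 and power 77%. The other two rows are unchanged at 77% and 90%. The upper end of the loss thus depends on drinking falling in both arms; a loss of about 13 points remains without it.

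**Simulation on skewed counts** (N = 384, correlation 0.55, 15% common fall, 20% reduction):

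| Counts | Change | Visit difference | Untransformed ANCOVA |
|---|---|---|---|
| Lognormal, CV 0.8 | 64% | 77% | 88% |
| Lognormal, CV 1.0 | 45% | 61% | 71% |
| Gamma-Poisson, CV 0.8 | 60% | 74% | 84% |
| Gamma-Poisson, CV 1.0 | 43% | 56% | 67% |

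ANCOVA gains 24 to 26 points on the change contrast and 10 to 11 on the visit difference. A quasi-Poisson model with robust standard errors adds 1 to 2 points to that.

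A further simulation with correlation 0.6 and N of 286 or 384 covered eight settings. The baseline-adjusted log-link Poisson model with robust standard errors beat the change contrast by about 23 to 29 points and the visit difference by about 11 to 17. Only about 0 to 3 of those points were beyond untransformed ANCOVA.

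**Log link without adjustment.** At 143 per arm, for a five-drink difference at a single visit (means 20 to 30, CV 0.6 to 1.2), a log-link model gains 0.3 to 1.4 points over the untransformed comparison.

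**Type I error.** The untransformed group-by-time contrast rejected in about 3.5 to 4% of null simulations.

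**The case against.** **A condensed article may leave modelling detail to an analysis plan not shown.** This stands for the scale of analysis. A reader might infer that the plan fixes an analysis of raw counts, but the text never says so, and a transformation could be specified elsewhere. It does not stand for baseline: the time factor is written out with month 0 as a level, and the primary analysis shows that the authors state covariate adjustment where they intend it.

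**The power loss should be blamed on using a normal-theory model instead of a count model.** A reader might infer this, but the figures do not bear it out. Most of the gap closes with ANCOVA on untransformed values. One count model did much better than the untransformed group-by-time test, a negative binomial mixed model (about 18 to 22 points). That held only under lognormal heterogeneity; under gamma heterogeneity its gain was about nil.

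**Unequal covariance between arms threatens the test.** With 1:1 allocation and the type I error found, this is not supported.

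**The inputs are assumed.** This stands in full. The article gives no mean, spread, skewness or baseline correlation for either count. The simulations covered weekly drinks and the between-arm contrasts, not the full three-outcome, four-wave MANOVA. The largest number of drinks on one occasion was not simulated separately. The variance argument applies to it, but the size depends on its own baseline correlation.

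**Conclusion.** The concern holds as a loss of precision on two secondary outcomes, caused by how baseline is used. Under the assumptions listed, the loss is roughly 11 to 29 power points: the lower part of the range if the planned contrasts are simple visit differences, the upper part if they are changes from baseline and drinking falls in both arms. The missing log link accounts for about 0 to 3 points. The direction does not depend on the choice between lognormal and gamma counts; the size depends on the baseline correlation and on which contrast is meant.

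The planned test remains valid, and the AUDIT-C primary analysis and the sample size are unaffected. A reader might infer that the trial is underpowered for its main question; nothing here supports that. The stepped contrasts are the reason to act, since a difference missed at six months also removes the comparisons at 12 and 24 months.

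**What to change.** Take the two drink counts out of the MANOVA and analyse each separately over 6, 12 and 24 months, by GEE or a mixed model. Include condition, time, condition by time and the baseline count as covariate, with robust standard errors.

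Because right skew is likely, a log-link quasi-Poisson model with log(baseline + 1) is a reasonable form, reporting the ratio of mean drinks (extended / minimal) with a 95% confidence interval at each visit. The negative binomial model should not be listed as interchangeable with it. When the true effect was an additive shift, it estimated a ratio of 0.760 against a true 0.798 (lognormal, CV 1.0) and 0.780 against 0.824 (gamma, CV 1.0). It also fell below untransformed ANCOVA in power in some gamma settings.

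AUDIT-C keeps its present scale and its primary ANCOVA. The cost is wording only: baseline values are already collected, and no participants are added. The small downside is that log-link results are ratios, not differences in drinks.

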The widespread accessibility of the Internet may prove it an ideal vehicle for the delivery of self-help material to problem drinkers. A recent systematic review [13] emphasized the fast growing body of evidence for the evidence supporting Internet-based Interventions (IBIs). The majority of this research suggests that personalized feedback interventions can reduce drinking over short intervals [14-17]. However, there is little research evaluating the efficacy of more comprehensive web-based interventions for facilitating long-term changes in drinking [18]. This limitation is notable for at least two reasons. First, initial changes in alcohol use are most often not sustained [19,20]; and the strategies needed to maintain long-term change may be different than those required for initial change [21-23]. Whereas personalized feedback could provide a source of initial motivation to reduce drinking, more comprehensive cognitive-behavioural strategies may be more effective for aiding in sustained behaviour change and relapse prevention. Second, there have been increasing calls to adapt efficacious alcohol treatments to allow for sustained delivery, consistent with a continuing care model of treatment [24-26]. One advantage of IBIs is that they can be sustained indefinitely (i.e., the cost of long-term or comprehensive interventions will often be comparable to those of brief interventions).

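### The stepped contrasts let a non-significant six-month result block the two-year drinking comparison, although the trial was sized for two years and its rationale is sustained change

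*Protocol article*

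**What the plan says.** All references are to the protocol article.

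- **Hypotheses.** Drinking outcomes at twelve months are primary. Six months (Secondary Hypothesis 1) and two years (Secondary Hypothesis 2) are secondary, and the two-year hypothesis carries no condition on six months.
- **Analysis plan: primary hypothesis testing.** On the twelve-month comparison: "This will be tested for the primary outcome variable, the AUDIT-C, using an analysis of covariance" with the baseline value as covariate. No earlier result has to be significant first.
- **Secondary analyses.** A group by time (0, 6, 12, 24 months) repeated measures MANOVA covers AUDIT-C, drinks in a typical week and the highest number of drinks on one occasion. Planned contrasts follow, and "significant differences must be observed at the six months’ time point before comparisons will be made between condition at the twelve months’ time point". The sentence ends in *etc.*; with 24 months the only remaining time, that takes the gate to two years.
- **Power analysis.** The trial is to be "powered to be able to detect a difference in 1 point on the AUDIT-C scale", and "sufficient participants will be recruited in order to test for a similar effect size at the two-year time point". Hence 480 are recruited, to allow for 40% loss at two years.
- **Background.** Normative feedback may give the first motivation, whereas "more comprehensive cognitive-behavioural strategies may be more effective for aiding in sustained behaviour change and relapse prevention".

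**The concern.** A fixed sequence is a sound way to control multiplicity, but this one starts at a secondary time point, and everything later depends on it.

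The comparator is itself a personalised feedback intervention. If feedback works early and the extended programme mainly helps people hold their gains, the arms could look alike at six months and separate later. In that case the rule forbids the two-year contrast, which is the only two-year drinking comparison between arms that the article describes. It also forbids the twelve-month contrasts on the two secondary drinking measures.

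Two further points follow. The Power analysis section makes no allowance for two earlier tests having to succeed before two years is reached. And twelve-month AUDIT-C has both an ungated primary test and a gated contrast, with nothing to say which governs if they disagree.

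**Working it through.** **Inputs from the Power analysis section.** Difference 1 point; SD 3.0 (pilot SD 2.5); power 80%; "hypotheses be tested at the .05 level of significance"; 143 per arm needed; 480 recruited; attrition 20% at twelve months and 40% at two years. So there are 240 per arm at baseline, 240 × 0.8 = 192 at twelve months and 240 × 0.6 = 144 at two years.

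**Assumptions not in the article.** Two-sided tests; six-month attrition 10 to 20% (216 to 192 per arm); between-wave outcome correlation ρ from 0 to 0.9; monotone dropout; observed cases; AUDIT-C only; no baseline adjustment.

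**Step 1: the plan's own figure.** n per arm = 2 × 3.0² × (1.960 + 0.842)² / 1² = 141.3, so 142. The t-test version gives 142.2, rounded up to 143 per arm, or 286 in all, as stated. A one-sided test would give 112, so two-sided .05 is what was used. Then 286 / 0.6 = 477, against 480 recruited (480 × 0.6 = 288 retained).

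**Step 2: each time point alone.** SE = 3.0 × √(2/n); power = Φ(1/SE − 1.96).

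| Time | n per arm | SE | Power |
|---|---|---|---|
| 6 months | 192 to 216 | 0.306 to 0.289 | 0.904 to 0.934 |
| 12 months | 192 | 0.306 | 0.904 |
| 24 months | 144 | 0.354 | 0.807 |

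**Step 3: the 6-12-24 chain.** The three z-statistics are multivariate normal with means d/SE and correlation ρ × √(n_later/n_earlier). Chain power is the probability that all three exceed 1.96. The effect at 12 and 24 months is held at 1 point.

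| Six-month effect | Two-year power through the chain, SD 3.0 |
|---|---|
| 1 point (constant) | 0.66 to 0.78 |
| 0.5 point | 0.27 to 0.40 |
| 0.25 point | 0.09 to 0.14 |
| 0 | about 0.02 |

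With the pilot SD of 2.5, a constant effect gives 0.88 to 0.915. A six-month effect of 0.5 point still gives only 0.45 to 0.54.

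**Step 4: alternatives, SD 3.0.** Two years ungated: 0.81. Two years gated only on a significant twelve-month test: 0.73 to 0.785, whatever the six-month effect. Under a constant effect, and setting like against like, that is about 1 point (0.785 against 0.777) to 7 points (0.73 against 0.66) better than the present chain. With a six-month effect of 0.5 point, it is 0.73 to 0.785 against 0.27 to 0.40.

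**Step 5: baseline adjustment on both sides.** With an assumed baseline correlation of 0.5, the SD becomes 3.0 × √(1 − 0.25) = 2.60. At ρ = 0.5 between the adjusted outcomes, the present chain gives 0.86 to 0.87 and the 12-then-24 order 0.88. Adjustment raises both; it does not separate them.

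**The case against.** A reader might infer that the six-month gate blocks the primary hypothesis, or that a late benefit cannot be tested at all. The article does not support that. The primary analysis of covariance has its own section with no precondition, and the gate sits under the secondary analyses, on contrasts that follow a MANOVA. A 1-point AUDIT-C benefit that emerges by twelve months is still tested at about 90% power. A secondary sequence that stops early does not cancel a primary result.

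A reader might also infer that the chain by itself leaves the two-year comparison badly underpowered. Under a constant effect the loss is moderate. It rests on SD 3.0, which the plan sets above the pilot value; at SD 2.5 the chain stays above 80%. Moving the start to twelve months recovers little in that case.

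The low figures need a six-month effect well below the planning value, and the article gives reasons to expect an early effect: the pilot's 1-point difference was seen at six months, Secondary Hypothesis 1 predicts a six-month benefit, and the pilot section frames the long-term question as whether reductions are sustained. Testing in time order, to see whether a difference appears and then persists, is coherent with that.

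These points limit the scope and the severity. They do not remove the problem. The Background leaves room for late separation, Secondary Hypothesis 2 is stated without condition, and the late-effect loss remains large at the pilot SD. An early effect being plausible is no reason to make the long-term test depend on it.

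**Conclusion.** The point holds for the two-year comparison and for the twelve-month contrasts on the secondary drinking outcomes. It does not hold for the primary twelve-month AUDIT-C test. For that comparison the fault is only that an ungated test and a gated contrast stand side by side with no rule of precedence.

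The order of testing costs a moderate amount of two-year power if the effect is constant (from 0.81 to between 0.66 and 0.78) and most of it if the effect emerges late. All chain figures depend on six-month attrition and between-wave correlation, which the article does not give, and on AUDIT-C alone, whereas the contrasts follow a three-outcome model. The plan should be changed here, but the primary result is not at risk.

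**What to change.** 1. Remove the six-month gate from the planned contrasts.
2. State that the twelve-month AUDIT-C analysis of covariance is the unconditional primary test and governs that comparison.
3. Choose one of two rules for two years: test it without a gate (power about 0.81), or gate it only on the primary twelve-month test (about 0.73 to 0.785 unadjusted). If a sequence is kept, six months comes after the later time points.
4. Restate two-year power for the chosen order, with baseline adjustment either applied throughout or left out throughout.
5. Report the adjusted differences with 95% confidence intervals at 6, 12 and 24 months whatever the tests show.

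The cost is a few sentences and no extra participants. By comparison, keeping the full 6-12-24 chain at 80% power under a constant effect would need about 530 to 564 recruits (correlation 0.7 to 0.3, 10% six-month attrition) instead of 480, and would still not protect against a late effect. The downside is small: in a sequence, the six-month claim can be made only if the later tests succeed, while an ungated two-year test gives up the multiplicity control that the sequence offered. The choice should be fixed before outcome data are seen.
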